## Background

Two-thirds of all cancer patients develop bone metastases during the course of their disease [1]. This form of distant relapse occurs from many types of solid cancers, especially from lung, breast, and prostate [2]. Bone involvement can also be extensive in certain hematologic malignancies [3, 4]. About 30% of all skeletal metastases and 10% of all primary bone tumors are located in the spinal column [5], mostly the lumbar (52%), thoracic (36%), and cervical (12%) spine [6]. The exact mechanism of bone metastasis is not fully understood. It is postulated that bone metastases arise as a detachment of tumor cells from the primary tumor and reach the bone by intravascular penetration, resulting in adhesion in distinct bone areas. The tumor cells cause local changes of the bone structure, caused by an imbalance of bone remodeling. Bone metastases present as osteoplastic, osteolytic, or mixed osteolytic/osteoplastic tumor masses. Many metastatic bone lesions cause few or no symptoms, but for skeletal-related events, pain is the most common symptom; many patients with bone metastasis experience significant pain at some point during their disease course [7]. Other skeletal-related events include reduce activity in daily life (ADL), decreased energy, hypercalcemia, and risk of pathological fractures and neurological deficits. Pathologic bone fractures occur in 5% and spinal cord compression in 10–15% [5]. Restrictions of movement of the spinal column may have a devastating long-term impact on function, mobility, independence, health, and quality of life (QoL). External beam radiotherapy has an established role in the management of patients with bone metastases of the spine. The fractionation schedule applying 30 Gray in ten fractions is a safe and effective treatment modality commonly used to achieve palliation of pain associated with spinal metastases [8]. In about 50–80% of the patients, a decrease of pain is reported and about 30% of the patients showed complete remission of pain [8]. Stereotactic body radiation therapy (SBRT) using intensity-modulated radiotherapy (IMRT) can be a safe treatment option for treating spinal metastasis with enhanced targeting accuracy [9, 10]. Published data report that IMRT to the spine was well tolerated, had no significant late toxicities, and spared other organs at risk [11]. Pre-treatment megavoltage computed tomography (CT) allows for the control of the patient position and improves treatment accuracy [12].

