### Recruitment and randomization

The patients will be given all the relevant information about the study by the radiation oncologist at their first presentation to our department (approximately 1–2 weeks before the start of RT). If patients are interested in participating in the study, they will receive a second appointment in order to further inform them and to obtain informed consent. A block randomization procedure will be used to ensure even distribution of patients into the four groups. The randomization procedure will be carried out by a central office. The study personnel responsible for the recruitment and patient care will have no access to the randomization information and the study director will have no influence on the recruitment of patients. The recruitment phase will be concluded with the attainment of the planned number of patients (120 patients in total, 30 patients in each group). Projected recruitment time will be 12 months, and recruitment is scheduled to start in February 2017. Regular study follow-up will end two years after enrolment or, where applicable, with the respective patient’s death.

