### Inclusion criteria

Patients with histologic confirmation of a tumor disease, demonstrating metachronic solitary or multiple metastatic bone lesions of the thoracic or lumbar spine or the sacral boneIndication for RT of the bone metastasesMRI-based staging examinations (if necessary)Age 18–85 yearsKarnofsky Index ≥ 50% [13]Signed declaration of informed consent

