### Assessment of the primary and secondary endpoints

The aim of the study is to evaluate local control rates in metastatic bone disease. The primary endpoint is defined by bone remodeling according to density in the metastasis. Bone density will be measured at the irradiated region at baseline and at the three-month time-point after the completion of RT (t_2_). Furthermore, the local control is assessed by CT imaging taken before and at three and six months after radiation treatment. Secondary endpoints are vertebral stability, QoL, fatigue, pain, overall survival, bone survival, pathological fracture, and neurological deficits. The baseline examination will be carried out immediately before the start of therapy and is scheduled to comprise the comprehensive recording of the socio-demographic data, the recording of the current pain situation (VAS score), the extent of fractures, the QoL, and the current degree of fatigue. The follow-up examinations will take place after the end of RT, as mentioned above (Fig. 1).

The secondary endpoints such as overall survival, fatigue, QoL, and anxiety will be recorded by using validated questionnaires (EORTC QLQ FA13 [14], EORTC QLQ BM22 [15], and the questionnaire to record stress in patients with cancer [FBK] according to Book et al. [16]). All patients will also be asked to record their pain history by using a pain diary (documentation of medication daily during treatment and once weekly after the completion of treatment, VAS pain scale). The pain response is documented on the VAS (range of 0–10). Complete response is defined as VAS score of 0/10 after three or six months and partial response is defined as a reduced value by at least 2 points after three or six months, according to the international consensus response categories by Chow et al. [17]. Overall survival is defined as time from initial diagnosis until death and bone survival is defined as time from initial diagnosis of irradiated spinal bone metastasis until death (Additional file 1).

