### Statistical analysis

Due to the explorative character of this study, it was not possible to estimate the total number of cases; with a scheduled number of 30 patients per group, it will, however, be possible to detect a standardized mean-value effect (Cohen’s d) of 0.74 with a power of 80% and a significance level of 5%, if a one-factorial variance analysis is calculated. All variables will be analyzed descriptively by tabulation of the measures of the empirical distributions. In case of continuous variables mean values, standard deviations, median, minimum, and maximum values will be documented. Categorical variables will be documented as occurrence and percentage. The primary endpoint will be measured by CT. Results will be presented at three months after completion of RT and differences between groups will be calculated using a one-factorial variance analysis. Differences of categorical variables will be calculated with the Chi-square test. The survival analysis will be performed using the Kaplan–Meier method and log-rank test.

All statistical analyses will be carried out descriptively using SAS software Version 9.4 or higher (SAS Institute, Cary, NC, USA).

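### The primary density comparison pools osteolytic, osteoplastic and mixed metastases with no lesion-type term and no stated favourable direction, so it can be imprecise and is hard to read as local control

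*Protocol article*

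**What the plan says.** All references are to the protocol article.

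- **Background** describes metastases as the result of a remodelling imbalance and names three presentations: "Bone metastases present as osteoplastic, osteolytic, or mixed osteolytic/osteoplastic tumor masses". On the source of the disease it says: "This form of distant relapse occurs from many types of solid cancers, especially from lung, breast, and prostate".
- **Inclusion criteria** open with "Patients with histologic confirmation of a tumor disease" and go on to lesions of the thoracic or lumbar spine or sacrum. No radiographic type is named. **Exclusion criteria** remove myeloma, lymphoma and sarcoma, but no lesion type.
- **Assessment of the primary and secondary endpoints** gives the aim, "The aim of the study is to evaluate local control rates in metastatic bone disease", and then the endpoint, "The primary endpoint is defined by bone remodeling according to density in the metastasis". On timing: "Bone density will be measured at the irradiated region at baseline and at the three-month time-point after the completion of RT". It does not say whether a rise or a fall is favourable, or whether this depends on lesion type. The same section adds that local control is also assessed by CT at three and six months.
- **Statistical analysis** presents results at three months, where "differences between groups will be calculated using a one-factorial variance analysis". The single factor is the treatment group. Neither lesion type nor baseline density is named as a term.
- **Recruitment and randomization**: "A block randomization procedure will be used to ensure even distribution of patients into the four groups". No stratification by lesion type is stated.
- **Discussion** names one subgroup analysis, and it concerns IMRT technique.

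**The concern.** Density stands in for local control. Osteolytic and osteoplastic lesions are imbalances of remodelling in opposite directions, so it is doubtful that a given change in density means the same in both. The stated model averages over both and does not separate them. Three things follow.

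1. **Meaning.** With no favourable direction stated, a difference in pooled mean density does not by itself say which arm controls tumour better.
2. **Dilution or cancellation.** If osteoplastic lesions respond less than lytic ones, or the other way, the pooled difference shrinks towards zero although the boost has an effect in one type.
3. **Precision.** If raw density differs strongly between types, that difference goes into the residual variance of a model that has only the treatment factor.

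This is not merely detail left to an analysis plan. The article itself fixes the primary variable and the one-factor model.

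**Working it through.** **The plan's own figure.** Statistical analysis states a detectable Cohen's d of 0.74 with 30 per group, 80% power and 5% significance. A two-sided two-sample t-test with n = 30 per group (noncentral t, 58 df) gives a detectable d of 0.736, and power at 0.74 of 80.5%. The figure reproduces as a pairwise comparison.

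**Inputs from the document.** Four arms of 30, two with boost and two without; 5% level; d = 0.74; one-factor ANOVA.

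**Assumptions (not in the document).** Two types only, 60% lytic and 40% osteoplastic. The boost raises density by 0.74 within-type SD in lytic lesions. The osteoplastic effect is +0.74, 0 or −0.74. Within-type SD is 1. The gap between type means is 2 SD on raw three-month density, or 0 as an approximation to change from baseline.

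**Average effect.** Pooled effect = 0.6 × 0.74 + 0.4 × (osteoplastic effect):
- shared: 0.74
- no osteoplastic response: 0.6 × 0.74 = 0.444
- opposite: 0.444 − 0.296 = 0.148

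**Variance.** A share q of osteoplastic lesions and a gap g add q(1 − q)g² to the residual variance. Here that is 1 + 0.4 × 0.6 × 4 = 1.96, so the SD is √1.96 = 1.40 and the detectable difference is 1.40 times larger. With an even split it is 1 + 4/4 = 2, a factor of 1.41.

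**Power of the four-arm omnibus test, by simulation:**

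| Osteoplastic effect | Gap 2 SD, pooled | Gap 2 SD, type as a factor | Gap 0, pooled |
|---|---|---|---|
| +0.74 (shared) | 65% | 93% | 93% |
| 0 | 31% | 47% | 47% |
| −0.74 | 8% | 8% | 8% |

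A rerun with 6,000 trials per row gave 65/93/93, 32/49/47 and 8/8/8 (the last cell 8.5%), so the figures hold to about 2 points. As a check by formula, the noncentral F (3 and 116 df, two arms against two, no gap) gives 93.2% at d = 0.74, 49.7% at 0.444 and 9.0% at 0.148.

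**Reading the table.** Adjusting for type recovers what the gap costs. It does not recover what cancellation costs: in the last row both models have 8%. There the type-specific estimates and the interaction show the effect. In the rerun the two-versus-two interaction test had about 97% power for opposite effects, but only about 49% when osteoplastic lesions do not respond.

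**Sensitivity to the mix.** For a pairwise comparison with 30 per group, no gap and opposite effects in a share q, d = 0.74(1 − 2q):
- q = 10%: d = 0.59, power 62%
- q = 20%: d = 0.44, power 39%
- q = 30%: d = 0.30, power 20%
- q = 50%: d = 0, power 5%

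If the share q shows no effect instead, d = 0.74(1 − q): q = 20% gives 62% and q = 50% gives 29%.

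**The case against.** The case on the other side is substantial, and most of it limits how far the point can go.

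- **The direction premise is inferred.** The article names three presentations but does not say how each responds to radiotherapy or which direction is good. If the effect is shared and there is no gap, the pooled omnibus test has 93% power and nothing is lost. This stands. The loss is a possibility with a range, not an established figure.
- **A reader might infer that the primary result is invalid or cannot be interpreted at all.** The document does not support that. Under randomisation the test of no effect on density holds its level: with a 2 SD gap and no effect, the ANOVA rejected in 4.4% of simulated trials. Local control is also assessed separately by CT. What is hard to read is pooled density as a measure of control.
- **A reader might infer that chance imbalance in lesion type would pass for a treatment effect.** The type I error already covers it. It costs precision: a 20-point imbalance with a 2 SD gap shifts that trial's difference by 0.2 × 2 = 0.4 SD, which adjustment would largely remove.
- **A reader might infer that restricting the primary analysis to lytic lesions lifts power from 32% to 87%.** Those figures come from different tests, a 3-df omnibus test and a 1-df boost contrast. Matched, with no osteoplastic response and a 2 SD gap, they are 31% against 71% (omnibus) or 46% against 86% (contrast). With a shared effect and no gap the restriction loses power: the boost contrast has 98% in all patients against about 87% in lytic lesions alone.
- **The gap penalty assumes raw three-month density.** Remodelling may mean change from baseline, in which a constant difference between types drops out. The article does not settle this. Cancellation is untouched either way.
- **The trial is exploratory, and covariates can be set in an analysis plan.** That lowers the urgency. But the article already names the primary model, and an exploratory density endpoint still needs a stated direction.

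**Conclusion.** The point holds in limited form. The stated primary analysis pools lesion types that the article itself distinguishes, with no type term and no favourable direction. It validly tests for an effect on density, but a pooled difference is hard to translate into local control if types respond differently, and a null result could hide an effect confined to one type.

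Under the assumptions above, leaving out lesion type costs about 28 points of omnibus power for a shared effect (93 − 65) and about 16 if osteoplastic lesions do not respond (47 − 31). It costs nothing if they move the opposite way, because both models then fail. The first two losses depend on a 2 SD gap in raw density and largely vanish if change is analysed. The lesion mix, the gap and the type-specific effects are all assumed. The change is worth making because it costs little, not because a loss has been shown.

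**What to change.** 1. Classify each irradiated lesion as predominantly osteolytic, mixed or osteoplastic from the existing baseline CT, by a reader blind to arm.
2. Include lesion type as a factor in the primary density model, together with baseline density, and say whether the outcome is the three-month value or the change.
3. Prespecify the treatment-by-type interaction and report the treatment difference within each type.
4. State for each type which direction of density change counts as favourable. The investigators have to supply this, since the article does not.
5. Keep all randomised patients in the primary analysis. Do not restrict it to lytic and mixed lesions.

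**Cost.** One variable read from images already taken, and a wording change. Of 120 − 4 = 116 residual df, type (2) and baseline density (1) leave 113, and the full interaction (3 × 2 = 6) leaves 107. The interaction test will have low power unless the types differ strongly, so the type-specific estimates should be shown with confidence intervals and not judged by that test alone.

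### Pain response is defined with no baseline-pain or analgesic condition, so patients pain-free throughout count as complete responders and falls reached on more medication count as response

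*Protocol article*

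**What the plan says.** The protocol article's section Assessment of the primary and secondary endpoints lists pain among the secondary endpoints and measures it on a 0–10 VAS. It sets out two response categories:

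- "Complete response is defined as VAS score of 0/10 after three or six months"
- "partial response is defined as a reduced value by at least 2 points after three or six months"

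It describes both as "according to the international consensus response categories", with a citation. The same section has a VAS score taken at baseline and asks patients to keep a pain diary, with "documentation of medication daily during treatment and once weekly after the completion of treatment, VAS pain scale".

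The nearest the Inclusion criteria come to pain is an indication for radiotherapy. Neither they nor the Exclusion criteria set a minimum VAS or require a painful lesion. The Background remarks: "Many metastatic bone lesions cause few or no symptoms". The Discussion names prevention of fractures and of neurological deficits among the goals of treatment, next to pain reduction. The Statistical analysis section assigns categorical variables to the Chi-square test.

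**The concern.** The complete-response rule looks only at the follow-up score. A patient without pain at entry who stays without pain meets it, although there was nothing to respond to. Radiotherapy can be indicated for reasons other than pain, so such patients can be enrolled.

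Both rules also look only at the score and not at how it was reached. A patient who goes from 6 to 4, or to 0, on heavier medication is a partial or complete responder. The medication record that could separate the two situations is collected but has no role in the stated rule.

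The response rates could then not be read as pain relief from radiotherapy. Pain-free patients add the same constant to every arm in expectation, which raises the rates and shrinks the contrast. Analgesic changes occur after allocation, so randomisation does not guarantee that they are balanced between arms.

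**Working it through.** The plan gives no expected rate, sample size or power for pain response, so there is no figure of its own to reproduce here. Its one design figure, a standardised difference of 0.74, concerns the continuous primary endpoint.

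**Step 1: apply the rule as written.**

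| Baseline VAS | Follow-up VAS | Analgesics | Class under the written rule |
|---|---|---|---|
| 0 | 0 | any | complete response |
| 1 | 0 | any | complete response |
| 6 | 4 | increased | partial response |
| 6 | 0 | increased | complete response |

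Pain-free patients can enter only through complete response, because a 2-point fall needs a baseline of at least 2. Increased medication can affect both categories.

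**Step 2: inflation of the complete-response rate.** Inputs:

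- True complete response among patients with pain: 30%, the Background's figure for complete pain remission.
- Share pain-free at baseline, p: not in the document; assumed 10, 20 or 30%.
- Share of those who stay at 0, s: not in the document; assumed 70 to 90%.

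Reported rate = (1 − p) × 0.30 + p × s.

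| p | s = 0.70 | s = 0.90 |
|---|---|---|
| 0.10 | 0.27 + 0.07 = 0.34 | 0.27 + 0.09 = 0.36 |
| 0.20 | 0.24 + 0.14 = 0.38 | 0.24 + 0.18 = 0.42 |
| 0.30 | 0.21 + 0.21 = 0.42 | 0.21 + 0.27 = 0.48 |

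**Step 3: chance imbalance.** If one arm of 30 has 3 more pain-free patients than another, in place of patients with pain, its expected rate moves by (3/30) × (s − 0.30):

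- s = 0.70: 0.10 × 0.40 = 4 points
- s = 0.90: 0.10 × 0.60 = 6 points
- s = 1.00: 0.10 × 0.70 = 7 points

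**Step 4: dilution of a difference.** Assume for illustration 30% against 60% complete response among patients with pain, the same p in both arms, and all pain-free patients staying at 0. The difference becomes (1 − p) × 30 points. Power is for a two-sided 5% comparison of two arms, by the normal approximation with pooled variance under the null:

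Φ{[Δ − 1.96 √(2p̄(1 − p̄)/n)] / √[(pA(1 − pA) + pB(1 − pB))/n]}

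Here pA and pB are the two arms' rates, Δ their difference and p̄ their mean.

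| p | Rates as written | Difference | Power, n = 30 per arm | Patients with pain only: n per arm | Power |
|---|---|---|---|---|---|
| 0 | 30% v 60% | 30 | 0.65 | 30 | 0.65 |
| 0.10 | 37% v 64% | 27 | 0.55 | 27 | 0.61 |
| 0.20 | 44% v 68% | 24 | 0.46 | 24 | 0.55 |
| 0.30 | 51% v 72% | 21 | 0.38 | 21 | 0.50 |

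In this scenario, dropping pain-free patients from the response analysis gains power despite the smaller denominator.

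**Step 5: analgesics.** The document gives no rate of analgesic change and no link between medication and VAS, so this part cannot be quantified.

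**The case against.** The strongest reply is that the definitions are tied to a cited international consensus and that the article only summarises it. The conditions may sit in that source, or in the full protocol or analysis plan, and a diary that records medication suggests that medication was meant to count. This limits the point but does not remove it. A reader might infer that the plan departs from the consensus, or has decided to disregard analgesics. The document supports neither, because the source is not shown. What it does show is a complete rule with thresholds, and that rule, followed as written, misclassifies the patients in the first, third and fourth rows of Step 1.

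The second reply concerns weight. Pain is one of several secondary endpoints in a trial that calls itself exploratory and analyses its data descriptively. That stands.

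Third, the Background remark on symptoms is about metastatic lesions in general, not patients selected for radiotherapy, and the same sentence calls pain the most common symptom. That also stands: the pain-free share among enrolled patients is unknown and may be small.

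Fourth, randomisation balances pain-free patients in expectation. This is right too. Their main effect is inflation and dilution; any shift between arms from them is a matter of chance.

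A reader might also object that a patient with baseline VAS 1 can never be a partial responder. That is no defect: such a patient's only possible improvement is to 0, which is a complete response.

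**Conclusion.** The point holds, at moderate severity. As written, the rule counts patients who are pain-free throughout as complete responders and ignores how a lower score was reached.

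Under the assumed pain-free shares of 10 to 30%, a true complete-response rate of 30% would be reported as 34% to 48%. A 30-point difference would shrink to between 27 and 21 points. The pain-free share, its persistence and the 60% comparator are assumptions; only the 30% is in the document.

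A reader might infer that 3 extra pain-free patients in an arm of 30 move its rate by 10 points, since 3/30 is 10%. That would require the patients they replace to have had no chance of response. With the 30% rate, the shift is 4 to 6 points, or 7 if all stay at 0. Nor does the point reach the primary endpoint, bone density at three months, or the sample size.

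**What to change.** Reword the pain-response definition as follows:

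- Limit the response analysis to patients with baseline VAS above 0, and require at least 2 at baseline to be eligible for partial response. A single cut-off of 2 for both categories would needlessly drop patients at VAS 1, who can reach complete response.
- Report patients who are pain-free at baseline separately, and report change in VAS for all patients.
- Count a response only where diary-recorded analgesic use has not increased from the pre-treatment entry or, failing that, the first diary entry, as far as the recorded medication data allow.

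The first two items use the VAS already collected. They cost a smaller denominator and less favourable response rates.

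The third needs some coding of diary entries and may need one new item. Analgesics are not listed among the baseline measurements, the diary is described from treatment onwards ("documentation of medication daily during treatment and once weekly after the completion of treatment"), and dose is not mentioned. A pre-treatment analgesic entry would be the clean solution; the first diary day is only a proxy.

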### Therapy drop-out criteria

Patient’s wishMedical condition requiring the discontinuation of therapy in the opinion of the study director or patientInsufficient compliance

In case of early drop-out from the study, the planned follow-up scheme will be continued. For non-evaluable patients, the reason will be recorded in the case report forms. Study patients will have the opportunity to refuse individual investigations.

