SBRT has been shown in prospective trials and numerous case series to be safe and effective for the treatment of spinal bone lesions as well as primary bone tumors. One comparison of the palliative efficacy and cost-effectiveness of external beam RT compared with SBRT as a primary treatment for spinal metastases found that patients treated with external beam RT had increased acute toxicities and there was a higher likelihood of them requiring further intervention at the treated sites. A recent trial showed that SIB-IMRT could be successfully applied to vertebral metastases with spinal cord compression in up to four consecutive vertebrae. Good ADL preservation and pain control were achieved with acceptable toxicity [20]. Lubgan et al. demonstrate excellent local control rate of 93% after 24 months in 33 patients who underwent SBRT with SIB. No radiation myelopathy occurred [21]. Nevertheless, the optimal dose schedule could not be found and no prospective trial has been investigated in this setting so far.

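### Pain response is scored by VAS at three or six months with no condition on further local treatment, so relief after re-irradiation or surgery of the treated vertebra counts for the schedule that failed

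*Protocol article*

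**What the plan says.** In the section *Assessment of the primary and secondary endpoints*, the protocol article lists pain among the secondary endpoints, has it documented on a 0–10 VAS, and prints two response rules:

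- Complete: "Complete response is defined as VAS score of 0/10 after three or six months".
- Partial: "partial response is defined as a reduced value by at least 2 points after three or six months".

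The categories are said to be "according to the international consensus response categories", but the article does not reproduce the content of those categories. A pain diary collects further data ("documentation of medication daily during treatment and once weekly after the completion of treatment, VAS pain scale"), but medication does not enter either printed rule.

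Neither rule carries a condition on re-irradiation, surgery or augmentation of the treated vertebra after randomisation. Re-intervention is not among the listed endpoints. The exclusion criteria rule out earlier radiotherapy to the area, but only at entry. The section *Therapy drop-out criteria* adds: "In case of early drop-out from the study, the planned follow-up scheme will be continued". That sentence concerns drop-out. It means VAS values continue to be collected, and it does not say how pain after re-treatment is counted.

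**The concern.** The response rule is meant to show what the randomised schedule achieved. As printed, it cannot separate relief from that schedule from relief produced by a second local treatment given because the first did not work. A patient in pain at three months who is then re-irradiated and reports VAS 0 at six months satisfies the complete-response rule. This is so whether the two visits are read as either-counts or are tabulated separately, because the six-month value qualifies in both cases.

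The error need not be equal across arms. If the boost works, there are more failures without it and so more patients who may be treated again. Crediting their later relief raises the response rate most where the first treatment did worst, and pulls the comparison with and without boost towards zero. A real benefit on pain could then look small or absent.

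**Working it through.** **The article's own figure.** No rate or power is stated for pain response. The only power statement, Cohen's d of 0.74 with 30 per group, 80% power and 5% significance, concerns the primary endpoint. It reproduces as a two-group, two-sided t comparison (detectable d = 0.736; power 80.5% at 0.74) and does not bear on this point.

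**Inputs from the article.** 120 patients, 30 per arm, hence 60 with and 60 without boost if pooled. Chi-square test for categorical variables. From the Background: "In about 50–80% of the patients, a decrease of pain is reported".

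**Assumed inputs (not in the article).** True response, meaning response without credit for re-intervention: 65% without boost (middle of 50–80%) and 80% with boost. Re-intervention before the visit, all among non-responders: 10–20% vs 3–5% of the arm. Share of these then meeting the VAS rule: s = 50–80%. Two-sided 5%.

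**Formulas.**

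- Observed response = true response + re-intervention rate × s.
- Power = Φ[(d − 1.96·se₀)/se₁], with se₀ from the pooled and se₁ from the separate proportions.

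**No re-intervention.** d = 0.15; se₀ = √(2 × 0.725 × 0.275/60) = 0.0815; se₁ = √[(0.65 × 0.35 + 0.80 × 0.20)/60] = 0.0804. Power = Φ[(0.15 − 0.1598)/0.0804] = Φ(−0.12) = 45%.

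**All corners of the assumed ranges, 60 vs 60:**

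| Re-intervention without / with boost | s | Observed response | Difference (points) | Power |
|---|---|---|---|---|
| 10% / 3% | 50% | 70.0% vs 81.5% | 11.5 | 31% |
| 10% / 3% | 80% | 73.0% vs 82.4% | 9.4 | 23% |
| 10% / 5% | 50% | 70.0% vs 82.5% | 12.5 | 36% |
| 10% / 5% | 80% | 73.0% vs 84.0% | 11.0 | 31% |
| 20% / 3% | 50% | 75.0% vs 81.5% | 6.5 | 14% |
| 20% / 3% | 80% | 81.0% vs 82.4% | 1.4 | 4% |
| 20% / 5% | 50% | 75.0% vs 82.5% | 7.5 | 17% |
| 20% / 5% | 80% | 81.0% vs 84.0% | 3.0 | 6% |

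The difference runs from 1.4 to 12.5 points and power from about 4% to 36%. The formula counts rejections in the right direction only. Adding the opposite tail makes the lowest value about 5%.

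A central case, 15% vs 5% with s = 65%: 0.65 + 0.15 × 0.65 = 0.748 and 0.80 + 0.05 × 0.65 = 0.833. The difference is 8.5 points and power 21%.

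**Lower re-intervention rates.**

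- 5% vs 2%: the difference is 13.5 points (s = 50%) or 12.6 points (s = 80%).
- 2% vs 1%: the loss is (0.02 − 0.01) × s = 0.5 to 0.8 points, and power stays at 42–43%.

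**Plausibility of the top end.** 20% of the arm is 20/35 = 57% of its non-responders, which is high.

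**A second set of assumptions, 30 vs 30.** True response is 50% vs 80% (the ends of the Background range; power 69%), with re-intervention now a share of non-responders.

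- 20% vs 5%, s = 50%: 0.50 + 0.50 × 0.20 × 0.50 = 55.0% and 0.80 + 0.20 × 0.05 × 0.50 = 80.5%; power 56%.
- 50% vs 10%, s = 70%: 67.5% vs 81.4%; power 23%.

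The direction is the same.

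**The case against.** The strongest reply is that this is a condensed article. The full protocol, the analysis plan, the additional file or the cited consensus categories may say how re-treated patients are scored. That is possible. But the article does not leave the definition to another document: it prints an explicit rule, and that rule taken as written gives the misattribution.

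Second, scoring VAS regardless of later treatment is a legitimate treatment-policy estimand. The alternative makes a clinician's decision to re-treat part of the outcome, and surgery or augmentation may follow fracture or instability rather than failed pain control. Both points stand. They are the reason to limit the non-responder rule to treatment given for pain or local failure, and to keep the VAS-regardless result alongside it.

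Third, the article names no pooled test of boost against no boost for pain, and even without bias the 65% vs 80% scenario has only 45% power. That also stands; the power figures only illustrate the scale of the loss.

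A reader might infer more than the article supports:

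- *That re-intervention is known to differ between these arms.* The Discussion reports that "there was a higher likelihood of them requiring further intervention at the treated sites", but that compares external beam radiotherapy with SBRT, and the Abstract describes all four arms as SBRT. It shows only that such events occur and can depend on the radiotherapy approach.
- *That local control on CT has the same fault.* The article prints no CT criteria for local control, so this cannot be tested.
- *That every re-treated patient becomes a responder.* Only those whose VAS reaches 0 or falls by at least 2 points do, and the partial rule also uses an earlier VAS value.
- *That the primary result is at risk.* The primary endpoint is bone density, which the pain rule does not touch.

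**Conclusion.** The point holds for the pain-response wording. The printed rule credits the randomised schedule with relief that follows further local treatment of the same vertebra, and nothing else in the article corrects this. If such treatment is more frequent in the weaker arms, the difference between arms is biased towards zero.

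How much is unknown, because the article gives no re-intervention rate. The loss could be most of a 15-point difference or less than 1 point, depending entirely on the assumed rates. Pain is one of several secondary endpoints in a trial that calls itself exploratory, so this is a defect in one definition that is worth repairing, and not a threat to the trial's main analysis.

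**What to change.** 1. Record the date, type and reason of any re-irradiation, surgery or augmentation of the treated vertebra.
2. Add to the response definition that a patient is scored as a non-responder from the date of such treatment when it is given for pain or local failure.
3. Report the proportion re-treated by arm.
4. Keep response by VAS regardless of re-intervention as a sensitivity analysis, so that both readings are visible.

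The cost is one case report form item and one sentence in the endpoint definition. Response rates may be slightly lower, and the decision to re-treat becomes part of the outcome. The article's trial status says recruitment was not complete, so the item could still be collected prospectively for later patients. The change concerns scoring only and sets no rule on when to re-treat.
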